#### Cost-effectiveness and cost-utility

To evaluate the economic effects of MIP and UC, relevant cost categories of resource use and volumes of these categories will be measured. Finally, volumes are multiplied by the corresponding costs.

The direct (non-)healthcare costs will be assessed with the Trimbos/iMTA questionnaire for Costs associated with Psychiatric Illness (Tic-P) [67]. This self-reporting questionnaire consists of 15 items and assesses healthcare use in a recall period of 3 months.

Productivity losses are assessed by the Short Form Health and Labor Questionnaire (SF-HLQ) [68]. The SF-HLQ measures the extent of production losses of paid and unpaid work in four modules: absence from work, reduced productivity at paid work, unpaid labor production, and impediments to paid and unpaid labor. It consists of 11 items.

For the cost valuation, standardized cost prices will be used from the Dutch manual for cost analysis in healthcare research [69]. Where no standard cost prices are available, real costs or tariffs will be used to estimate costs. Productivity losses will be calculated based on the friction costs method. Cost prices will be presented in Euros and the baseline year is 2012, or otherwise discounted. The discounting rate of costs is 4%, and 1.5% for effects [70]. To analyze differences in costs, costs per patient-year will be calculated.

For the cost-effectiveness analysis (CEA), costs will be weighted against the primary outcome measure participation. The measure is described above.

For the cost-utility analysis (CUA), costs per year will be weighed against utilities based on the SF-36. The SF-36 is a reliable and valid instrument to measure health-related quality of life [71]. Utilities are values or preferences that respondents assign to a particular health state and are overall expressed on a scale ranging from 0 to 1 [72]. The utilities used in this study will be derived with an algorithm of the SF-6D, which estimates utilities based on the health-related quality of life scores of the SF-36 [73]. Furthermore, the utilities will be estimated by an algorithm of Brazier, Roberts, and Deverill (2002). The derived utilities at three measurement points (T0, T2, T4) will be used to compute the Quality Adjusted Life Years (QALY) score by means of the area under the curve method [74]. This means that the weights for each health state (utilities) will be multiplied by the time in that particular health state and then summed to calculate the total number of QALYs.

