### Data collection

For the (cost-) effectiveness evaluation, measurements will be carried out before the first MIP/UC pre-treatment sessions (T0), after the MIP/UC (T1 = post pre-treatment), after the regular multidisciplinary pre-rehabilitation assessment (before starting rehabilitation), at the start of the pain rehabilitation treatment (T2), after treatment completion (T3), and at 6-month follow-up (T4). Study assessments at T0, T2, and T3 will be integrated in current care clinical assessment battery pre-rehabilitation and post rehabilitation (see also Figure 1 (flow-chart) and Table 2). Cost measurements will be carried out at three points: T0, T2, and T4. Information on drop-out from and adherence to the (pre-) rehabilitation treatment, start and end date of the treatment, and no show are derived from the administrative patient registry.

**Table 2 T2:** Outcome measures, abbreviation instrument, and assessment moments PREPARE study

		**Baseline**	**Two sessions**	**After pre-treatment**	**Start pain rehab treatment**	**Finish pain rehab treatment**	**6 months after T3**
	**Abbr.**	**T0**^**a**^		**T1**	**T2**^**a**^	**T3**^**a**^	**T4**

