***Cost-effectiveness evaluation***							
Cost questionnaire	Tic-P	x			x		x
Productivity losses	SF-HLQ	x			x		x
Quality of life/health status	SF-36	x			x	x	x

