### Economic evaluation

In the economic evaluation, cost and effects of usual care and MIP will be calculated and compared. Therefore, the cost per patient year (=participant year) will be calculated. This means that all observed costs will be extrapolated to a 1-year period.

The analysis will include those persons for whom at least two of the three follow-up measurements (cost diaries) are available.

For the cost-effectiveness analysis (CEA) the cost-effectiveness ratio will be stated in terms of costs per improvement on participation (as assessed with the USER-P).

For the cost-utility analysis (CUA) the cost-utility ration will be stated based on the cost per (Quality Adjusted Life Year) QALY gained.

Bootstrap (5,000 times) re-sampling techniques will be used to test for differences and uncertainty in costs and effects between the MIP and the UC intervention.

The bootstrapped cost-effectiveness and cost-utility ratios will be subsequently plotted in a cost-effectiveness and cost-utility plane. The results of this study will also be depicted in cost-effectiveness acceptability curves (CEACs) [104].

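### The QALY calculation leaves out the SF-36 collected at T3, and as described it sets costs scaled to one year against QALYs summed over a variable follow-up time

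*Protocol article*

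**What the plan says.** In the protocol article, the section on cost-effectiveness and cost-utility derives SF-6D utilities from the SF-36 and then says: "The derived utilities at three measurement points (T0, T2, T4) will be used to compute the Quality Adjusted Life Years (QALY) score". The method is the area under the curve, with utilities "multiplied by the time in that particular health state and then summed to calculate the total number of QALYs". No reason is given for stopping at three points.

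In Table 2, the row "Quality of life/health status" has four crosses: T0, T2, T3 and T4. The PDI, VAS and PSC rows have the same pattern.

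On costs, the Data collection section says: "Cost measurements will be carried out at three points: T0, T2, and T4". The Economic evaluation section adds that "all observed costs will be extrapolated to a 1-year period". The cost-utility comparison is described as "costs per year will be weighed against utilities based on the SF-36", and the ratio is to be stated as "the cost per (Quality Adjusted Life Year) QALY gained".

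On timing, the text below Table 2 says that the wait between T1 and T2 varies and that rehabilitation lasts 10 to 16 weeks. T4 is 6 months after T3.

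**The concern.** There are two separate problems.

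First, T2 to T4 covers the whole rehabilitation programme and the six months after it. A utility curve may well bend there, and T3 is the only measurement inside that interval. Without it, the area rests on linear interpolation between T2 and T4 although an observed value is available. A between-arm gain that is present at T3 and gone by T4 would count as nothing.

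Second, a cost-per-QALY ratio needs both parts on one time base. Here the cost is yearly, while the QALY is described as a total over whatever time elapsed between T0 and T4. That time differs between patients, and a patient followed for longer accumulates more QALYs through longer observation alone.

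At stake is the cost-utility answer, which is part of the second main research question. The primary participation outcome is not affected.

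**Working it through.** The article gives no QALY, cost or cost-per-QALY figure, so there is nothing to reproduce. The check is what the stated rules imply.

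**Inputs**
- a = weeks from T2 to T3: 10 to 16 (Data collection, text below Table 2); 13 is the midpoint.
- T3 to T4: 6 months, taken as 26 weeks. T2 to T4 is therefore 10 + 26 = 36 to 16 + 26 = 42 weeks.
- T0 to T2: not given, and variable. Values used below are assumptions.
- g2, g3, g4 = between-arm utility differences at T2, T3 and T4: not given, so treated as scenarios.

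**Step 1: leaving out T3**

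Area from T2 to T4, in utility-weeks:
- with T3: ½(g2 + g3)·a + ½(g3 + g4)·26
- without T3: ½(g2 + g4)·(a + 26)

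The first minus the second equals ½(a + 26) times the distance of g3 from the straight line joining g2 and g4. The error is therefore zero only when g3 lies on that line.

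With a = 13 and g2 = 0 (and no difference at T0, so T0 to T2 contributes nothing):

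| T3 difference | With T3 | Without T3 | Without / with |
|---|---|---|---|
| g3 = g4 | 6.5 + 26 = 32.5·g4 | 19.5·g4 | 60% |
| g3 = g4/3 | 2.17 + 17.33 = 19.5·g4 | 19.5·g4 | 100% |
| g3 = 0 | 13·g4 | 19.5·g4 | 150% |

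Across a = 10 to 16 weeks:
- g3 = g4: 18/31 = 58% to 21/34 = 62%.
- g3 = 0: 18/13 = 138% to 21/13 = 162%.
- No error: g3/g4 = a/(a + 26), which is 10/36 = 0.28 to 16/42 = 0.38.

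The pre-treatment is given before T2, so g2 need not be zero. With a = 13:
- g2 = g4/2 and g3 = g4: with T3, 9.75 + 26 = 35.75·g4; without, ½ × 1.5 × 39 = 29.25·g4. The T2 to T4 area is understated by 18%.
- g2 = g3 = g4: no error.

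**Step 2: time base**

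Let C be the yearly cost difference and Q the QALY difference summed over D weeks.
- As written: C / Q.
- Both per patient-year: C / (Q × 52/D).
- The first divided by the second: 52/D.

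This takes one D for all patients and holds however C was brought to a year.

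| Assumed T0 to T2 (weeks) | a (weeks) | D (weeks) | 52/D |
|---|---|---|---|
| 4 | 10 | 40 | 1.30 |
| 13 | 13 | 52 | 1.00 |
| 16 | 16 | 58 | 0.90 |
| 26 | 16 | 68 | 0.76 |

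**Step 3: both together** (a = 13, g2 = 0)

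The factor on cost per QALY is 52/D multiplied by the with/without ratio from Step 1.
- D = 43 (assumed wait 4 weeks): 1.21 × 1.67 = 2.02 for g3 = g4; 1.21 for g3 = g4/3; 1.21 × 0.67 = 0.81 for g3 = 0.
- D = 65 (assumed wait 26 weeks): 1.33, 0.80 and 0.53 in the same order.

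**The case against.** T0, T2 and T4 are also the cost measurement points, so the choice is coherent. That stands as an explanation, but utilities need not be taken only when costs are, and the T3 value is scheduled anyway.

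A reader might infer that the plan understates the QALY gain by about 40%. The documents do not support that. It requires no arm difference at T2 and equal differences at T3 and T4, and other paths give no error or an overstatement. The protocol's own statements on timing concern participation rather than utility, and they do not settle the path: Hypothesis 1a expects a difference both after rehabilitation and at six months, while the text below Table 2 expects the relevant change at six months.

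A reader might also infer that the T3 SF-36 is discarded altogether. It is left out of the QALY only. Quality of life is a listed secondary outcome, and the effect evaluation assesses all outcomes at each follow-up moment.

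On the time base, a condensed article may leave a later annualisation of QALYs to the full protocol, and the text does not rule one out. That stands: the mismatch is what the rules imply as written, not proof of what will be done. Nor can a 30% inflation be read from the documents. A D of 40 weeks leaves only 4 weeks from T0 to T2 for two sessions, the waiting list and the pre-rehabilitation assessment, even with the shortest treatment. Because the cost questionnaire recalls 3 months, observed costs also do not span T0 to T4. The 52/D factor therefore describes the mismatch of time bases, not how costs are gathered.

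**Conclusion.** The point holds, without a fixed direction or size. The SF-36 is scheduled at T3 and the stated QALY rule omits it. Costs are annualised, and no matching step is stated for QALYs over a T0 to T4 period that the protocol itself calls variable.

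Both effects vanish together only by coincidence: a T3 difference on the T2 to T4 line and a follow-up of about 52 weeks, or two errors that happen to cancel. Every figure above depends on an assumed utility path, and those for the time base also on an assumed T0 to T2 interval. They show that the ratio is sensitive, not that it will be wrong by a given amount.

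The matter is worth correcting before analysis but is confined to the secondary economic evaluation.

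**What to change.** Replace the three-point rule with an area under the curve through T0, T2, T3 and T4, using each patient's actual assessment dates.

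Then state one time base for the ratio: express both costs and QALYs per patient-year, dividing each patient's QALY total by the observed years from T0 to T4. A common fixed period from T0 is less suitable, because T4 is tied to the end of treatment and some patients would need extrapolation to reach it.

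The cost is a change of analysis wording. The T3 SF-36 is already scheduled, and no extra assessment is needed.

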### Statistical analysis

The statistical analysis for the effect evaluation, the cost-effectiveness evaluation and cost-utility analysis, and the process evaluation will be described separately. Data will be analyzed using SPSS version 17.

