#### Effect evaluation

Baseline data will be analyzed to describe the characteristics of all participants and to check for significant imbalances between the two groups. Possible baseline differences between the intervention group and the control group will be tested by an independent samples *t*-test (normal distribution) or Mann–Whitney U tests (non-normal distribution) in the case of continuous variables. In the case of dichotomous variables, a Chi-square test will be used. In case of imbalances in prognostic factors between both randomized groups, an adjustment for those factors will take place. The number of drop-outs and follow-up losses in both groups will be reported based on descriptive data. Differences in primary and secondary outcome measures between MIP and UC will be analyzed using repeated measurements techniques and multilevel analysis. This approach is chosen because repeated measures within individual subjects are taken. A *P* value <0.05 is considered statistically significant. Data will be analyzed according to the intention-to-treat principle. All outcomes will be assessed at each follow-up moment by taking into account a specific a priori hypothesis. Additionally, per protocol analyses will be performed to assess whether protocol deviations have caused bias.

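### No adjustment for T0 utility is stated for the incremental QALY, which as written carries any chance T0 difference and is less precise than the collected data allow

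*Protocol article*

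**What the plan says.** Under Cost-effectiveness and cost-utility, SF-36 responses are converted to SF-6D utilities. Those from T0, T2 and T4 "will be used to compute the Quality Adjusted Life Years (QALY) score by means of the area under the curve method", which the article explains as utilities "multiplied by the time in that particular health state and then summed to calculate the total number of QALYs". The patient-level quantity is thus a total that includes T0 utility, not a change from baseline.

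Under Economic evaluation, the cost-utility ratio is "stated based on the cost per (Quality Adjusted Life Year) QALY gained". The comparison of arms is given in one sentence: "Bootstrap (5,000 times) re-sampling techniques will be used to test for differences and uncertainty in costs and effects between the MIP and the UC intervention". Resampled ratios feed the planes and the acceptability curves. No covariate is named at any of these steps.

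The article's only baseline-adjustment rule is under Effect evaluation: "In case of imbalances in prognostic factors between both randomized groups, an adjustment for those factors will take place". The opening of Statistical analysis says: "The statistical analysis for the effect evaluation, the cost-effectiveness evaluation and cost-utility analysis, and the process evaluation will be described separately". Table 2 schedules the SF-36 at T0, T2, T3 and T4, so baseline utility will be available.

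**The concern.** T0 utility enters a QALY total in two ways: directly, through the first trapezium, and indirectly, because later utilities are correlated with it. If the arms differ at T0 by chance, part of that difference appears as QALYs gained or lost. Randomization is blocked by hospital only, so nothing in the design balances T0 utility beyond chance.

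The incremental QALY is the denominator of the cost-utility ratio, and cost-utility belongs to the second main research question. What is at stake is how precise that quantity is, and how far it reflects the luck of allocation at baseline.

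**Working it through.** **The plan's own figures.** The article gives none for the QALY comparison. Its sample size does reproduce: a difference of 5, SD 10, two-sided 0.05 and 80% power give 63.8, so 64 per arm by the t-test. Then 128/0.8 = 160. I use 64 evaluable patients per arm.

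**Inputs from the article.** Rehabilitation (T2 to T3) lasts 10 to 16 weeks; T3 to T4 is 6 months (26 weeks).

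**Assumed inputs.** T0 to T2 of 4, 12 or 26 weeks; utility SD 0.10 to 0.15, equal at all visits; one common correlation of 0.3, 0.5 or 0.7 between visits; the same intervals for every patient.

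**Formulas.** Let a = T0–T2 and b = T2–T4, in years.
- Trapezium weights on (T0, T2, T4): w = (a/2, (a+b)/2, b/2).
- Variance of the total in units of SD²: V = w′Rw, where R is the correlation matrix.
- Slope of the total on T0 utility: c = w₁ + ρ(w₂ + w₃).
- Squared correlation of the total with T0 utility: r² = c²/V.
- Unadjusted SE = SD·√(2V/n); adjusted SE = unadjusted SE·√(1 − r²).

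**One case in full** (a = 12 weeks, b = 10 + 26 = 36 weeks, ρ = 0.5, SD 0.10, n = 64):
- w = (6, 24, 18)/52 = (0.115, 0.462, 0.346); T0 has 12.5% of the weight.
- V = 0.346 + 0.253 = 0.599; c = 0.115 + 0.5 × 0.808 = 0.519; r² = 0.519²/0.599 = 0.45.
- Unadjusted SE = 0.10 × √(2 × 0.599/64) = 0.0137.
- Adjusted SE = 0.0137 × √0.55 = 0.0101, which is 26% narrower.
- A T0 difference of one standard error, 0.10 × √(2/64) = 0.0177, moves the unadjusted incremental QALY by 0.519 × 0.0177 = 0.009.

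**Over the whole grid.**

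| Quantity | Range |
|---|---|
| Direct weight of T0 in the total | 4% to 21% |
| SE of the T0 difference, 64 per arm | 0.018 to 0.027 |
| Shift in incremental QALY from a T0 difference of 0.02 | 0.005 to 0.020 |
| Unadjusted SE | 0.011 to 0.031 |
| Adjusted SE | 0.008 to 0.021 |
| Narrowing of the interval, ρ = 0.3 to 0.7 | 9% to 47% |
| Narrowing of the interval, ρ = 0.5 | 21% to 32% |

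**Unequal correlations.** Correlation may fall with distance in time. Take the case above with T0–T2 0.5, T0–T4 0.3 and T2–T4 0.5:
- c = 0.115 + 0.231 + 0.104 = 0.450.
- V = 0.346 + 2 × (0.0266 + 0.0120 + 0.0799) = 0.583.
- r² = 0.347, and the narrowing is 1 − √0.653 = 19%.

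The gain is smaller than the 26% under a common correlation, but it remains.

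**The case against.** The strongest reply is that this is inferred from silence. No sentence calls the comparison unadjusted. Bootstrapping measures uncertainty and is fully compatible with a regression in each resample. A journal article may leave the covariates of a health-economic model to the full protocol or analysis plan. This stands in part: a reader might infer that the article prescribes an unadjusted comparison, and it does not. But the article fixes the utility algorithm, the time points, the integration rule, the number of resamples and the outputs. Someone following those steps would compare totals with no T0 term.

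Second, the rule under Effect evaluation might be taken to cover the QALY comparison. Describing the analyses separately is a matter of layout and does not exclude it. But nothing says that it carries over, and it is conditional. Read with the baseline tests described just before it, it would leave a one-standard-error T0 difference (test statistic about 1) unadjusted, and it would not secure the gain in precision.

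Third, a reader might infer that the cost-utility result is biased. The documents do not support that. Allocation is randomized, so the unadjusted difference is unbiased in expectation, and its bootstrap interval already reflects chance T0 variation. The economic analysis is limited to persons with enough cost measurements, and randomization protects that subset less fully. But the article offers no ground for expecting a T0 difference in either direction.

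**Conclusion.** The point holds as a matter of precision and prespecification. As written, the economic evaluation compares QALY totals that contain T0 utility and states no adjustment for it. The estimate is unbiased in expectation, carries any chance T0 difference, and uses the collected data less efficiently than it could.

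Adjustment would narrow the interval by roughly 9% to 47%, and by about 21% to 32% at a common correlation of 0.5. These figures rest on the assumed correlations and T0–T2 gap; the SEs in QALY units rest also on the assumed SD. None of these is in the article. The figures concern the incremental QALY only. The effect on the ratio and the acceptability curve, which depend on costs as well, was not calculated.

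A reader might go further and infer that a chance T0 difference would decide the sign of the result. The article states no expected QALY difference, so that cannot be shown, and chance could still decide the sign of a small effect after adjustment. The primary outcome and the sample size of 128, inflated to 160, are unaffected.

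**What to change.** Add a sentence under Economic evaluation: in each bootstrap sample, the incremental QALY is estimated by linear regression of the QALY total on arm, T0 utility and hospital (the factor within which randomization is blocked). Use that estimate for the cost-utility ratio, the plane and the acceptability curve, and report the unadjusted difference as secondary. If the full protocol or analysis plan already says this, confirming it is enough.

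The cost is that sentence and one regression line in the bootstrap program. No new data are needed. No patient with a computable total is lost, because the area under the curve already requires T0 utility. Fixing the rule in advance also removes a later choice between adjusted and unadjusted results.

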#### MI-specific possible active ingredients

Resulting from the existing literature on MI, potential specific active ingredients were identified and will be assessed in this study [75,76].

The stage of change is assessed by the Multidimensional Pain Readiness to Change Questionnaire 2 (short version). It measures the chronic pain participants’ readiness to change. The questionnaire is based upon the trans theoretical model of behavior change of Prochaska and DiClemente. The MPRCQ2-26 consists of 26 items and is scored on a seven-point Likert scale [77]. Psychometric properties are evaluated and appeared to be satisfactory [78]. To be able to take it into account as possible moderator, it is measured before and after the pre-treatment.

MI integrity is hypothesized to be another working mechanism for MI. It is further explained below under the heading ‘MI integrity and fidelity’.

#### Possible moderators

We will also measure specific individual factors at baseline that could influence the treatment effect. From the literature, a number of psychosocial attributes moderating the effects of the pain rehabilitation treatment are identified [79].

Research has shown the influential role of expectancy on treatment outcome in pain rehabilitation [80,81]. Credibility and expectancy is measured by an adapted and translated version of the Credibility and Expectancy Questionnaire (CEQ) [82]. In two parts, participants are asked to rate in total five items related to the credibility and expectancy regarding pain rehabilitation treatment. Credibility and expectancies regarding the treatment have to be rated in two items. In another item the expected success in terms of an improvement in participation, decrease in disability, and decrease in pain intensity are rated. The CEQ uses a rating scale, ranging from 1 (not at all) to 9 (very much). Good psychometric properties have been demonstrated and the same factors structure was confirmed [82].

Motivation is assessed by the Treatment Motivation Questionnaire (TMQ). The TMQ assesses intrinsic and extrinsic information about entering and remaining in treatment [83]. It consists of 26 items to be rated on a five-point Likert scale ranging from 1 (not at all true) up to 5 (very much true). The factors internal and external motivation, interpersonal help seeking and confidence in treatment are represented. Items are slightly adapted to the rehabilitation context. The TMQ correlates well with professionals’ rating of the abovementioned factors what suggests good construct validity [83].

Depressive symptoms are hypothesized to moderate the effects of the rehabilitation outcomes. Therefore, the level of depression is assessed by the Becks Depression Inventory (BDI) [84]. The BDI is a well-known instrument, and suitable for its use in pain research. It is a reliable, valid, and widely-used instrument [85,86].

Acceptance has shown to explain a significant amount of variance in the prediction of patient functioning and suffering from chronic pain [87]. Acceptance is assessed by the 10-item Acceptance and Action Questionnaire-II (AAQ-II) [88] and scored on seven-point Likert scale items ranging from ‘never be true’ up to ‘always true’. The Dutch version has shown a high internal consistency and a good validity [89].

Flexible goal-adjustment (FGA) has shown to be a moderator in the relation between self-discrepancies and negative emotions [90]; flexibility has shown to be of moderating influence on pain willingness and activity engagement [91]. FGA, a component of psychological flexibility is measured with the Tenacious Goal Pursuit and Flexible Goal Adjustment Scale Brandstädter and Renner Questionnaire [92], which assesses the tendency to adjust personal goals and standards to situational limitations. It consists of 15 items with five possible answers ranging from ‘totally agree’ up to ‘not agree at all’. The scale’s internal consistency is satisfactory (α = 0.80) [92].

